#### Secondary outcomes

3.7.2

(1) Delirium severity, assessed using the Memorial Delirium Assessment Scale (MDAS), and total delirium duration (number of days with a positive 3D-CAM assessment).(2) Quality of recovery- 15 (QoR-15) score on postoperative day 3.(3) Plasma levels of inflammatory biomarkers (procalcitonin, C-reactive protein, interleukin-6, lymphocyte-to-monocyte ratio [LMR], neutrophil-to-lymphocyte ratio [NLR]) at baseline, postoperative day 1, and postoperative day 3.(4) Postoperative pain intensity (NRS) trajectories and total opioid consumption (morphine milligram equivalents) over 48 h.(5) Incidence of postoperative complications (Clavien-Dindo classification) and length of hospital stay.

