#### Active intervention (SGB group)

3.4.1

Patients in this group will receive two stellate ganglion blocks: The first block will be performed on the afternoon before surgery. The second will be performed 30 min before the induction of general anesthesia on the day of surgery.

Lateralization: All blocks will be performed on the right side at the C6 level. The right side is selected for the following reasons: (1) right-sided SGB is associated with a lower risk of esophageal injury and has a more predictable anatomical relationship between the stellate ganglion and adjacent structures; (2) right-sided sympathetic blockade may have a more favorable effect on cardiac autonomic balance (reducing sympathetic outflow to the heart) compared to left-sided block; (3) previous pilot studies on SGB for perioperative neurocognitive outcomes predominantly used right-sided approach, facilitating comparison with existing literature.

Under sterile conditions and real-time ultrasound guidance (C6 level), a 22-gage needle will be advanced to the prevertebral fascia. After negative aspiration, 3–5 mL of 0.375% ropivacaine will be injected (Figure 2). Successful blockade will be confirmed by the development of Horner’s syndrome (ptosis, miosis, anhidrosis) and/or ipsilateral skin temperature increase ≥1.5 °C within 15 min.

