### Outcome measures

3.7

A summary of the assessment schedule is provided in Table 1 (SPIRIT).

**Table 1 tab1:** SPIRIT schedule of enrolment, interventions, and assessments (23).

Study period	Enrolment	Intervention		Postoperative period (daily: POD1-3)	Close-out
Timepoint	≤7 d pre-op	Day-1 p.m.	Day 0	POD1-3	D/C
Enrolment					
Eligibility screen	X				
Informed consent	X				
Interventions					
SGB/Sham block		X	X		
Surgery and standardized care			X		
Data collection					
Demographics, medical history	X				
MoCA	X				
ASA physical status	X				
Outcome measures					
Primary outcome					
POD incidence (3D-CAM)				X (POD1-3 bid)^a^	
Secondary outcomes					
Delirium severity (MDAS)^b^				X (POD1-3 bid)^b^	X (record)
Quality of recovery-15 (QoR-15)				X (on POD3)	
Inflammatory biomarkers (procalcitonin, CRP, IL-6, LMR, NLR)^c^	X (blood)			X (on POD1 and POD3)^c^	
Postop pain intensity (NRS)^d^				X (q8h, POD1-2)^d^	
Opioid consumption (MME)^d^				X (total, POD1-2)^d^	
Postop complications (Clavien-Dindo)^e^				X (daily)^e^	X (record)
Length of hospital stay (days)					X
Safety monitoring					
Adverse events (AEs)		X	X	X (daily)	X

a POD incidence (3D-CAM): assessed twice daily (bid) from postoperative day 1 to day 3.

b Delirium severity score: assessed daily (POD1-3). Total delirium duration is recorded at discharge (D/C).

c Inflammatory biomarkers: blood samples collected at baseline (V0), postoperative day 1, and postoperative day 3.

d Postop pain and opioid use: pain intensity (NRS) is assessed every 8 h (q8h) for the first 48 h only (POD1-2). Total opioid consumption (MME) is calculated and recorded for the first 48 h (POD1-2).

e Postop complications: monitored daily (POD1-7) and recorded at discharge.

D/C, discharge; SGB, stellate ganglion block; MoCA, Montreal Cognitive Assessment; ASA, American Society of Anesthesiologists; POD, postoperative day; 3D-CAM, 3-Minute Diagnostic Interview for CAM-defined Delirium; QoR-15, quality of recovery-15 scale; CRP, C-reactive protein; IL-6, interleukin-6; NRS, numerical rating scale; MME, morphine milligram equivalents; bid, twice daily; q8h, every 8 h.

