### Sample size calculation

3.8

Based on prior literature reporting POD incidences ranging from 35 to 48% (2–4), we adopted a best-case scenario assumption for sample size planning: a baseline incidence of 40% in the sham group and a 50% relative risk reduction (to 20%) in the SGB group. Under these assumptions (*α* = 0.05, power = 80%, two-sided Chi-square test), 78 patients per group are required. Accounting for an estimated 10% dropout rate, the final sample size is 174 participants (87 per group).

We acknowledge that this effect size may be optimistic, especially given that our protocol excludes patients with preexisting cognitive impairment and includes a multicomponent delirium prevention bundle. If the true effect is smaller, this study may be underpowered for the primary outcome. Therefore, the results should be interpreted as hypothesis-generating, and future meta-analyses will be needed to confirm smaller effects.

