#### Analysis of primary outcomes

3.9.2

The cumulative incidence of POD on postoperative days 1–3 will be compared between groups using the Chi-square test, and relative risk (RR) with a 95% confidence interval (CI) will be reported. A supplementary multivariable logistic regression will be performed to adjust for pre-specified covariates: age, baseline MoCA score, and ASA physical status. To obtain adjusted relative risk instead of odds ratio, modified Poisson regression with robust standard errors will be adopted for covariate-adjusted analysis. Multivariable logistic regression will be used only as a supplementary approach when convergence issues occur.

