#### Analysis of secondary outcomes

3.9.3

Continuous secondary outcomes measured at a single time point (e.g., total QoR-15 score on postoperative day 3, length of hospital stay) will be compared between groups using independent Student’s t-tests if data are normally distributed, or Mann–Whitney *U* tests if the normality assumption is violated. Normality will be assessed using the Shapiro–Wilk test and homoscedasticity using Levene’s test.

For longitudinal data collected at multiple time points (e.g., serial pain NRS scores every 8 h for 48 h, inflammatory biomarkers on POD1 and POD3), we will employ linear mixed-effects models with a random intercept for each patient to account for within-subject correlation. Fixed effects will include treatment group, time, and their interaction term. A significant interaction term would indicate different trajectories of change between groups.

Total opioid consumption over the first 48 postoperative hours (in morphine milligram equivalents, MME) is a count variable and will be analyzed using Poisson regression or negative binomial regression if overdispersion is present. Results will be expressed as incidence rate ratios (IRRs) with 95% confidence intervals. Overdispersion will be verified via Pearson chi-square divided by degrees of freedom. Baseline pain score, operation duration and body weight will be adjusted in regression models. Model fitness will be evaluated by AIC and deviance.

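### QoR-15 is collected only on postoperative day 3 and compared without a pre-block score, an avoidable loss of precision on one secondary outcome

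*Protocol article*

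**What the plan says.** Section 2.2 lists postoperative recovery among the secondary objectives and names QoR-15 as its only measure. Section 3.7.2, item (2), defines the outcome as "QoR-15) score on postoperative day 3". Table 1 agrees: the QoR-15 row carries one mark, on postoperative day 3, and its enrolment, day-before-surgery and day-of-surgery cells are empty.

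Section 3.9.3 treats it as an outcome with one time point, giving "total QoR-15 score on postoperative day 3, length of hospital stay" as its examples. Such outcomes "will be compared between groups using independent Student’s t-tests if data are normally distributed", and otherwise by the Mann–Whitney U test. No covariate is named for this comparison.

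Other measurements do have a pre-treatment value. For the biomarkers, a footnote to Table 1 says "blood samples collected at baseline (V0), postoperative day 1, and postoperative day 3". MoCA is taken at enrolment and used in section 3.9.2, where the supplementary model for delirium is to "adjust for pre-specified covariates: age, baseline MoCA score, and ASA physical status". That list, and the longer one in section 3.6.4, are both stated for delirium, and neither contains a QoR-15 score.

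**The concern.** Older cancer patients of ASA class I to III can be expected to differ in comfort, sleep, anxiety and function before any block is given. The documents give no figure for this, so it is an assumption, though a mild one. Whatever part of the day-3 score reflects those earlier differences stays in the error term when the groups are compared without a baseline.

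The schedule itself causes this, so it is more than a detail that an analysis plan could settle later. No analysis plan can adjust for a score that was never collected, and a pre-block score cannot be obtained once the block has been given. At stake is the precision of the recovery comparison, which must also pass Benjamini–Hochberg control alongside the other secondary outcomes (section 3.9.5). A smaller point is that the multiple imputation in section 3.9.4 would have no earlier value on the same scale for a patient whose day-3 score is missing.

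**Working it through.** **Inputs from the protocol**

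- Section 3.8: 40% against 20% delirium, two-sided α = 0.05, power 80%, 78 per group, 10% dropout, 174 in total (87 per group).
- Evaluable patients expected: 2 × 78 = 156.
- The protocol gives no standard deviation, effect size, power or baseline correlation for QoR-15.

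**The plan's own figure.** The sample size concerns delirium only, but it supplies the number of patients to work with. With the unpooled normal approximation,

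n per group = (1.960 + 0.842)² × (0.4 × 0.6 + 0.2 × 0.8) / 0.2² = 7.849 × 0.40 / 0.04 = 78.5.

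This rounds up to 79, so the stated 78 is reproduced to within one patient. Then 78 / 0.9 = 86.7, giving 87 per group and 174 in total, as stated.

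**Effect of a baseline covariate.** Let r be the correlation between the pre-block and day-3 scores within groups. r is assumed.

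- Error variance left after ANCOVA = (1 − r²) × the unadjusted variance.
- Equivalent number of unadjusted evaluable patients = 156 / (1 − r²).
- Difference detectable with 80% power, unadjusted, 78 per group: (1.960 + 0.842) × √(2/78) = 0.449 SD. With ANCOVA this is multiplied by √(1 − r²).
- Power with ANCOVA at an effect of 0.449 SD: Φ(2.802 / √(1 − r²) − 1.960).

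| Assumed r | Error variance removed | Equivalent evaluable patients (instead of 156) | Detectable difference (SD) | Power at 0.449 SD |
|---|---|---|---|---|
| 0 | 0% | 156 | 0.449 | 80.0% |
| 0.2 | 4% | 163 | 0.440 | 81.6% |
| 0.3 | 9% | 171 | 0.428 | 83.6% |
| 0.4 | 16% | 186 | 0.411 | 86.4% |
| 0.5 | 25% | 208 | 0.389 | 89.9% |

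The patient equivalents use 156, because 174 already includes the allowance for dropout. The formulas assume a linear relation with a common slope, ignore the one degree of freedom spent on the covariate, and describe the comparison of means. They are only a guide if the Mann–Whitney test would have been used.

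**Can a baseline be collected?** Table 1 places enrolment within 7 days before surgery. Section 3.4.1 says "The first block will be performed on the afternoon before surgery". An enrolment score would therefore come before any study treatment, at a visit that already includes MoCA and a blood sample.

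**The case against.** The strongest reply is that nothing here is wrong or contradictory. The outcome definition, the schedule and the analysis agree with each other. Allocation is 1:1 at random, so an unadjusted comparison of day-3 scores is unbiased and its test is valid. The outcome is the day-3 score and not a change from baseline, and ANCOVA would estimate the same between-group difference. All of this stands. A reader might infer that the missing baseline biases the recovery result, or that recovery cannot be compared without each patient's starting point. The documents support neither.

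A reader might also link this point to the protocol's admission that the trial may be underpowered. Section 3.8 makes that admission for the primary outcome, and its calculation ("power = 80%, two-sided Chi-square test), 78 patients per group are required") is for delirium. A QoR-15 baseline does nothing for delirium power, and the protocol sets no power target for QoR-15 that could be missed.

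The gain also depends entirely on an assumed correlation. Enrolment may be up to a week before a major resection, and nothing in the documents shows that r exceeds 0.3. At r of 0.2 to 0.3, power moves only from 80% to between 81.6% and 83.6%. That limits the size of the point but does not remove it, since the measurement is cheap and cannot be recovered later.

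The imputation argument is modest. Section 3.9.4 already includes group, the primary outcome, the pre-specified covariates and time-point information, and patients who cannot answer on day 3 may be missing mainly because of their postoperative state. A same-scale baseline would add some information, but how much is not known.

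**Conclusion.** The point holds as an avoidable loss of precision on a single secondary outcome. The day-3 comparison remains valid, and the primary outcome is unaffected. If r lies between 0.2 and 0.5, the plan leaves 4% to 25% of the day-3 variance in the error term that a baseline score would remove. At the upper end, 156 evaluable patients would be worth about 208; at r of 0.3 or less, at most about 171. The range rests on an assumed correlation, on 78 evaluable patients per group, and on a linear covariance model. This is a worthwhile refinement of minor weight. The protocol gives no reason for leaving QoR-15 without a baseline when other measures have one.

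**What to change.** 1. In Table 1, add a QoR-15 mark in the enrolment column, to be completed before the first block.
2. In section 3.9.3, take QoR-15 out of the t-test or Mann–Whitney rule. Analyse the day-3 score by ANCOVA with group and baseline QoR-15 in the model, and use robust standard errors if the residuals are non-normal, so that no switch of test is needed.
3. In section 3.9.4, include baseline QoR-15 in the imputation model. This helps with missing day-3 scores and also covers any participant blocked before the change, whose baseline score would be imputed. Section 3.1.1 reports that no one had been enrolled at submission, so there may be few or none, but recruitment was planned from 5 February 2026 and this should be checked.

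The cost is a 15-item questionnaire of a few minutes per patient at an existing visit, one form field, and a minor amendment notified as section 3.11 requires where it counts as important. No extra staff or procedure is needed, and the primary analysis does not change.

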#### Safety outcomes

3.7.3

All adverse events (AEs), particularly SGB-related (e.g., hoarseness, dysphagia, hematoma, local anesthetic systemic toxicity) and opioid-related AEs (e.g., respiratory depression, nausea/vomiting), will be recorded.

### Sample size calculation

3.8

Based on prior literature reporting POD incidences ranging from 35 to 48% (2–4), we adopted a best-case scenario assumption for sample size planning: a baseline incidence of 40% in the sham group and a 50% relative risk reduction (to 20%) in the SGB group. Under these assumptions (*α* = 0.05, power = 80%, two-sided Chi-square test), 78 patients per group are required. Accounting for an estimated 10% dropout rate, the final sample size is 174 participants (87 per group).

We acknowledge that this effect size may be optimistic, especially given that our protocol excludes patients with preexisting cognitive impairment and includes a multicomponent delirium prevention bundle. If the true effect is smaller, this study may be underpowered for the primary outcome. Therefore, the results should be interpreted as hypothesis-generating, and future meta-analyses will be needed to confirm smaller effects.

### Statistical analysis

3.9

#### Analysis sets

3.9.1

The primary analysis will follow the intention-to-treat (ITT) principle, including all randomized participants in their originally assigned groups. A per-protocol (PP) population will also be defined for sensitivity analysis, excluding participants with major protocol deviations (e.g., failure to receive the assigned block, surgery duration outside predefined limits, or missing all primary outcome assessments).

#### Analysis of primary outcomes

3.9.2

The cumulative incidence of POD on postoperative days 1–3 will be compared between groups using the Chi-square test, and relative risk (RR) with a 95% confidence interval (CI) will be reported. A supplementary multivariable logistic regression will be performed to adjust for pre-specified covariates: age, baseline MoCA score, and ASA physical status. To obtain adjusted relative risk instead of odds ratio, modified Poisson regression with robust standard errors will be adopted for covariate-adjusted analysis. Multivariable logistic regression will be used only as a supplementary approach when convergence issues occur.

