#### Control of confounding variables

3.6.4

To minimize the potential impact of confounding variables on the primary outcome (POD incidence), the following measures will be implemented:

(1) Standardized perioperative management: As described in sections 3.5.1–3.5.3, all patients (both groups) will receive identical anesthesia, analgesia, and delirium prevention protocols. Any deviation from these protocols will be recorded as a protocol deviation.(2) Data collection on potential confounders: The following predefined variables, known to influence POD risk, will be collected and adjusted for in the statistical analysis: age, sex, body mass index (BMI), ASA physical status, baseline MoCA score, duration of surgery, intraoperative blood loss, intraoperative use of vasopressors, and postoperative opioid consumption (MME).(3) Statistical adjustment: In addition to the primary intention-to-treat analysis, a multivariable logistic regression model will be used to adjust for the above confounders, reporting adjusted odds ratios (aOR) with 95% confidence intervals.(4) Sensitivity analysis: A sensitivity analysis excluding patients with major protocol deviations (e.g., those who did not receive the allocated block, or those with incomplete primary outcome data) will be performed to assess the robustness of the findings.

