#### Handling of missing data

3.9.4

Missing data will be addressed using multiple imputation by chained equations (MICE). We will generate *m* = 50 imputed datasets, including the intervention group, primary outcome, and all pre-specified covariates in the imputation model. Pooled estimates will be obtained using Rubin’s rules. Missing POD assessments are assumed to be missing at random. Longitudinal time-point information will be included in the imputation model. Complete-case analysis will be conducted as sensitivity analysis to verify the robustness of primary results.

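### The unadjusted chi-square primary test is valid but probably gives up some precision, because the planned RR model adjusted for age, MoCA and ASA is only supplementary

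*Protocol article*

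**What the plan says.** Section 3.9.2 defines the primary comparison: cumulative POD incidence on days 1 to 3 "will be compared between groups using the Chi-square test", and the result is given as an RR with its 95% interval. The same section then adds: "A supplementary multivariable logistic regression will be performed to adjust for pre-specified covariates: age, baseline MoCA score, and ASA physical status". So that the adjusted result is a relative risk, it states that "modified Poisson regression with robust standard errors will be adopted for covariate-adjusted analysis", with logistic regression as the fallback if convergence fails.

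Section 3.6.4 gives the reason for adjusting: "The following predefined variables, known to influence POD risk, will be collected and adjusted for in the statistical analysis: age, sex, body mass index (BMI", and the list goes on to include ASA status and baseline MoCA. It also places adjustment beside the main result: "In addition to the primary intention-to-treat analysis, a multivariable logistic regression model will be used to adjust for the above confounders".

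Table 1 puts demographics, MoCA and ASA status at enrolment, before either block. Section 3.8 bases the sample size on the unadjusted test: "power = 80%, two-sided Chi-square test), 78 patients per group are required". Section 3.3 describes permuted blocks of 4 and 6 and names no stratification factor. On missing data, section 3.9.4 says "Pooled estimates will be obtained using" Rubin's rules, over 50 imputed data sets.

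**The concern.** The trial has one decisive test, at two-sided 0.05, and that test uses none of the baseline information that the plan already collects. If age, MoCA and ASA predict delirium, a model containing them gives a tighter estimate of the same relative risk. It also corrects for chance imbalance in those variables, which unstratified randomisation leaves open.

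Power has little slack. Sections 3.8 and 4 concede that the assumed halving of risk may be optimistic. The better-suited model is already specified, on the same scale as the crude estimate, but has supplementary status. If crude and adjusted results were to differ, the headline would be the one that leaves out factors the plan itself regards as influential.

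**Working it through.** **Inputs.** From section 3.8: risks 0.40 and 0.20, two-sided alpha 0.05, power 80%, 78 per group, 10% dropout, 174 in total. From section 3.9.2: chi-square as the primary test; modified Poisson with age, MoCA and ASA as the adjusted model. The prognostic strength of the covariates is not in the document, so it is assumed over a range.

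**Step 1: reproduce the plan's figure.** With unpooled variance, n = (1.960 + 0.842)² × [0.4×0.6 + 0.2×0.8] / 0.2² = 7.849 × 0.40 / 0.04 = 78.49. The stated 78 agrees to within rounding. Dropout: 78 / 0.9 = 86.7, so 87 per group and 174 in total, exactly as stated. At 78 per group the normal approximation gives 79.8% power with unpooled variance and 78.4% with pooled variance, the form that matches the chi-square test. At 87 per group the pooled figure is 82.7%.

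**Step 2: simulate the adjusted test.** There were 6,000 trials per scenario with 78 per arm. Three baseline covariates had equal weight in a logistic data model, with marginal risks of 0.40 and 0.20. Each trial was analysed by chi-square and by modified Poisson with robust standard error. AUC is the combined discrimination of the three covariates.

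| Assumed AUC | Power, chi-square | Power, adjusted | Change (points) | SE of log RR, adjusted / crude |
|---|---|---|---|---|
| 0.50 | 78.9% | 77.6% | -1.3 | 0.999 |
| 0.61 | 79.8% | 79.6% | -0.2 | 0.988 |
| 0.66 | 79.0% | 79.8% | +0.8 | 0.974 |
| 0.70 | 78.9% | 81.6% | +2.7 | 0.958 |
| 0.74 | 78.3% | 82.7% | +4.4 | 0.942 |
| 0.78 | 79.3% | 85.6% | +6.3 | 0.920 |

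The Monte Carlo standard error of each power figure is about √(0.8×0.2/6000) = 0.5 points. Under the null (30% in both arms) rejection was 4.7 to 5.6% for chi-square and 4.5 to 5.8% for the adjusted test. In the scenario giving 5.8%, chi-square gave 5.6%.

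**Step 3: compare with other runs.** A separate simulation of 4,000 trials per scenario gave -0.4 points for modified Poisson at AUC 0.66 (79.7% to 79.3%) and +1.4 for standardised logistic regression (78.3% to 79.7%). At AUC 0.78 it gave +5.1 (78.8% to 83.9%) and +7.5 (78.1% to 85.6%). A third run put the whole range at about -2 to +6 points. A small-sample correction to the robust standard error lowers adjusted power by a further 1.2 to 1.6 points in every row of the table, so the variance form matters.

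**Step 4: what it means for the interval.** Around an RR of 0.50 at AUC 0.78, the crude SE of 0.2721 gives 0.5 × exp(±1.96 × 0.2721) = 0.29 to 0.85. The adjusted SE of 0.2502 gives 0.31 to 0.82. At AUC 0.66 the SE falls only from 0.2720 to 0.2649, and the interval hardly moves.

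**Step 5: the interim look.** With 43 per arm, the 0.003 boundary of section 3.9.6, no treatment effect and 20,000 trials per scenario, there was no inflation. With weak or useless covariates, however, modified Poisson rejected in only 0.07 to 0.21% of trials, against 0.18 to 0.34% for chi-square.

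**The case against.** The strongest reply is that nothing is broken. An unadjusted chi-square in a 1:1 randomised trial holds its type I error, matches the sample-size basis and ignores no stratification factor. The adjusted RR will be reported anyway, so only the label of primary moves. All of this stands: the point is one of efficiency, and a reader who inferred that the primary test is invalid would go beyond the document.

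The reply is also right on four narrower matters.

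- The gain is conditional. Gains above about 3 points need an assumed AUC of roughly 0.74 or more. The eligibility criteria narrow all three covariates: age 60 or over, ASA I to III, and MoCA not below the cutoff.
- A reader might take these three to be the strongest risk factors. Section 3.6.4 lists nine variables and ranks none.
- A reader might think that Rubin's rules favour the adjusted model, because a chi-square p-value does not pool as an estimate does. The crude log RR and its standard error pool equally well, so the imputation plan gives no reason to adjust.
- The conceded risk of low power comes from an optimistic effect size, and a change of a point or two does not cure that.

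What the reply does not answer is why a pre-specified baseline model, on the same RR scale and with the same type I error, should stay supplementary when its likely effect is favourable and its cost is small.

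**Conclusion.** The point holds as a conditional improvement in efficiency. At 78 per arm and 40% versus 20%, adjusting for age, baseline MoCA and ASA narrows the standard error of the log RR by about 0 to 8%. It changes power by between about -2 points (no prognostic value) and +6 points (AUC about 0.78). At AUC 0.61 to 0.66 the change is within about 1.5 points either way. Type I error stays near 5%.

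These figures rest on an assumed covariate strength, on three covariates of equal weight in a logistic data model, and on complete data for 78 per arm. The document does not support the unconditional reading that the trial certainly loses precision: with weak covariates there is nothing to gain, and a small loss is possible.

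**What to change.** In section 3.9.2, make the RR adjusted for age, baseline MoCA and ASA the primary estimate and test at the final analysis. Use either modified Poisson regression with robust standard errors or standardised logistic regression, and name one. Pool it over the imputed data sets. Fix in advance the form of each covariate (for example, whether ASA enters as categories) and of the variance estimator. Keep the chi-square and crude RR as supportive. Restrict the model to these three baseline variables: the longer list in section 3.6.4 contains variables measured after randomisation, which do not belong in the primary model. If the adjusted test is also to be used at the interim look, check its behaviour at the 0.003 boundary first.

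The cost is wording in sections 3.9.2 and 3.6.4, with no new data. Section 3.1.1 reports no enrolment at submission; the change should in any case be settled before anyone sees unblinded outcomes. The downsides are a slightly less simple headline test, a power loss of up to about 2 points if the covariates carry no information (somewhat more with a small-sample variance correction), and possible conservatism of the robust test at the interim boundary.
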